#### **2.4.2 Faecal elastase**

Participants will also be asked to provide spot stool samples and FE-1 concentrations will be measured by Chemical pathology service at Southampton General Hospital using a commercially available ELISA kit. Results will be expressed as  $\mu\text{g/g}$  of stool. Patients will be provided with a specimen pot in advance of attending for testing so the sample can be delivered to the lab when they attend for the study. Alternatively, a pot can be taken home and then posted back to chemical pathology service when a sample is available.

Cut-offs for FE-1 values indicative of PEI have been established previously (Erikson *et al*, 2008), with values  $<200\mu\text{g/g}$  stool indicating PEI and values  $<100\mu\text{g/g}$  stool indicating severe PEI. We will consider the performance of both cut-offs in predicting PDAC. We will consider the inclusion of these cut-offs and the continuous value separately in multivariable logistic regression with cPDR values.

#### **2.4.3 Metabolomic analysis**

Serum and plasma samples will be collected, stored and later analysed for each participant to build a profile of proteomics and lipidomics for each cohort to determine if a specific profile exists in those with resectable PDAC compared to the other cohorts.

### **2.5 General principles for reporting and analysis**

95% confidence intervals will be presented throughout the report. Summary statistics will be presented as counts and percentages for categorical variables, or measures of spread for continuous variables (count, mean, standard deviation, median, IQR, minimum, maximum).

#### **2.5.1 Model building**

Logistic regression models will be constructed predicting PDAC status using  $^{13}\text{C}$ -mixed triglyceride breath test and faecal elastase values as described in section 2.4. Multivariable logistic regression models will then be constructed with the aim of finding the best-fitting combination of cut-offs for the  $^{13}\text{C}$  and faecal elastase values.

### **3 Planned analyses and reporting**

#### **3.1 Disposition of the study population**

Patient disposition will be summarised in a CONSORT flow diagram, showing a clear account of all patients who entered the study. These will be based on the enrolled population and will include:

- The number of patients assessed for eligibility and reason for not entering study
- The start and stop date of recruitment
- The number of patients in each cohort
- The number of early withdrawals, and reason for withdrawal

#### **3.2 Baseline and demographic characteristics**

In order to describe the three cohorts, demographic characteristics will be summarised with counts and percentages or measures of central tendency (mean, SD, median, IQR, range) as appropriate.

#### **3.3 Primary endpoint**

##### **3.3.1 Pancreatic cancer diagnosis**

The primary endpoint for this study is the prediction of PDAC. PDAC status is known at recruitment (i.e. all participants in the PDAC cohort are positive, all others are negative). Several logistic multivariable models will be constructed using results from the C-mixed triglyceride breath test and fecal elastase tests, with appropriate data transformations as outlined in section 2.4. All final regression model results will be reported. Models will be validated and adjusted for optimism using bootstrapping techniques (Steyerberg *et al*, 2001). Performance measures include sensitivity, specificity, positive predictive value, and negative predictive value. In order to evaluate these, numerous cut-offs for defining predicted cancer positivity in the underlying risk score will be evaluated with the study team. Discrimination will be measured using the R2 and D statistic. Calibration will be assessed visually with the aid of calibration plots, comparing observed and predicted risks in each tenth of predicted risk.

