## 1.4 Objectives

- 1) Can the  $^{13}\text{C}$ -mixed triglyceride breath test and the measurement of faecal elastase-1 be used to distinguish between patients with PDAC and healthy volunteers?
- 2) Do the 1, 2, and 3-hour  $^{13}\text{C}$ -mixed triglyceride breath tests perform similarly in their ability to classify PDAC patients in comparison to the 4-hour test?

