## **1.5 Definition of primary endpoint**

### **1.5.1 Pancreatic adenocarcinoma diagnosis**

The primary endpoint for this study is a prediction for stage I or II pancreatic adenocarcinoma (PDAC) vs a prediction of no PDAC.

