## **2 Statistical considerations**

### **2.1 Definition of analysis populations**

#### **2.1.1 PDAC population**

The PDAC population will consist of 25 participants with a known diagnosis of PDAC.

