#### **2.1.3 Chronic pancreatitis population**

The chronic pancreatitis population will consist of up to 10 participants with a known diagnosis of chronic pancreatitis but no known diagnosis of PDAC.

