### **2.4 Definition of key derived variables**

#### **2.4.1 The cumulative % $^{13}\text{C}$ -dose recovered (cPDR) during exhalation over the study period**

After an overnight fast for 12hrs, each participant will be asked to provide 2 baseline breath samples by blowing into  $2 \times 10\text{ml}$  exetainer tubes through a straw while wearing a facemask before they are given orally 250mg of 2- $^{13}\text{C}$ -octanoyl-1,3-distearin ( $^{13}\text{C}$ -MTG -Cambridge Isotope Laboratories, Andover, MA,

USA) together with a solid test meal consisting of 12g of butter on top of a single crispbake and 200ml water. After the test meal is given to each participant, post-prandial breath samples will be then collected every 30mins for 4 hours. After providing breath samples for 4 hours, participants will then be provided with a light meal and then asked to go home. The collected breath samples from the  $^{13}\text{C}$ -MTG breath test will be then analysed for the ratio of  $^{13}\text{CO}_2$  to  $^{12}\text{CO}_2$  by [name] using a Continuous Flow Isotope Ratio Mass Spectrometer (CF-IRMS SERCON Ltd, Crewe, UK) at the Southampton Centre for Biomedical Research Mass Spectrometry (SCBR mass spectrometry). The increase in  $^{13}\text{CO}_2$  content with regard to the baseline value of the initial breath sample is expressed as atom % excess and we will express the results of the  $^{13}\text{C}$ -MTG breath test as the cumulative percentage of  $^{13}\text{C}$ -label recovered on breath every 30 minutes until the 4 hour time point (240 minutes).

Normal values for  $^{13}\text{C}$  exhalation have been defined in healthy volunteers previously (Keller *et al*, 2014). Participants will be classified as exhibiting pancreatic exocrine insufficiency (PEI) if their cumulative  $^{13}\text{C}$  exhalation is below 1.6%, 4.2%, 7.9% or 13.8% at the 1, 2, 3 and 4-hour time points respectively. We will also consider defining cut-offs for PEI based on the mean values for the healthy controls at the respective time points, and the intervening 30-minute time points. We will also examine which cut-off for PEI best discriminates between PDAC and other participants at each time point in this study using the Youden index.

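### Section 3.3.1 pools chronic pancreatitis with healthy controls as negatives, so no planned model answers Objective 1 and specificity depends on how many pancreatitis patients are recruited

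*SAP*

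**What the plan says.** Objective 1 (SAP Section 1.4) asks whether the breath test and faecal elastase can "be used to distinguish between patients with PDAC and healthy volunteers". The sample size in Section 1.8 is 25 per group for the same two groups, and chronic pancreatitis plays no part in it.

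Section 2.1 defines three populations. The PDAC group is "25 participants with a known diagnosis of PDAC". The healthy controls number 25 and are matched to the cases on age and sex. The third group is "up to 10 participants with a known diagnosis of chronic pancreatitis but no known diagnosis of PDAC", and no matching is mentioned for it.

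The primary analysis in Section 3.3.1 reduces these three groups to two: "all participants in the PDAC cohort are positive, all others are negative". Section 2.4.1 makes the same reduction when it looks for the breath-test cut-off that "best discriminates between PDAC and other participants at each time point in this study using the Youden index".

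Section 3.4 summarises by cohort the breath-test distribution, the proportion below the Section 2.4.1 cut-offs and the faecal elastase distribution. Section 3.5 says that nothing further will be reported.

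On stage, Section 1.5.1 defines the endpoint as "a prediction for stage I or II pancreatic adenocarcinoma (PDAC) vs a prediction of no PDAC". Sections 2.1.1 and 3.3.1 define cases by cohort and state no stage. Section 2.4.3 refers to resectable disease.

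**The concern.** Both tests measure exocrine function of the pancreas, not cancer. A participant with chronic pancreatitis may have low results for reasons unrelated to a tumour, so the two kinds of negative may well have different false-positive rates. Once they are pooled, specificity is a weighted average of the two, and the weight is the number of pancreatitis participants who happen to be recruited, which may be anything from 0 to 10. The Youden cut-offs and the regression coefficients are estimated on the same mixture. The bootstrap correction in Section 3.3.1 deals with overfitting and does nothing about a mixed reference group.

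At stake is whether the trial reports an answer to its own first objective. The SAP plans no model restricted to PDAC and healthy controls, and Section 3.5 closes off additional analyses. An analyst who follows the plan would report figures that describe neither PDAC versus healthy nor PDAC versus pancreatitis. Adding the missing model later would be the kind of post hoc decision that Section 1.1 sets out to avoid.

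**Working it through.** **The plan's own figure.** Section 1.8 gives 25 per group, a difference of 17.8, an SD of 10.5 (stated for the cancer group; assumed here for both groups) and a two-sided 5% level. The non-centrality is 17.8 / (10.5 × √(2/25)) = 5.99. Power is 0.99995 by the non-central t with 48 degrees of freedom and 0.99997 by the normal approximation, so the stated 100% reproduces. It applies to PDAC versus healthy, not to the pooled comparison.

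**Make-up of the negatives.** Let m be the number of pancreatitis participants (Section 2.1.3: 0 to 10). Their share of the negatives is m/(25 + m), and the case fraction is 25/(50 + m).

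| m | Share of negatives | Case fraction |
|---|---|---|
| 0 | 0% | 50.0% |
| 5 | 5/30 = 16.7% | 25/55 = 45.5% |
| 10 | 10/35 = 28.6% | 25/60 = 41.7% |

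**Pooled specificity.** Write Sp_H for specificity in healthy controls and Sp_CP for specificity in pancreatitis. Then pooled specificity = (25 × Sp_H + m × Sp_CP) / (25 + m). The SAP gives neither value, so the following are assumptions. With Sp_H = 0.80 and Sp_CP = 0.30:

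- m = 0: 0.80
- m = 5: (20 + 1.5)/30 = 0.717
- m = 10: (20 + 3)/35 = 0.657

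At m = 10 with Sp_H = 0.80, Sp_CP = 0.20 gives 22/35 = 0.629 and Sp_CP = 0.60 gives 26/35 = 0.743.

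**Range.** The fall from m = 0 to m = 10 is (10/35) × (Sp_H − Sp_CP). For Sp_H from 0.80 to 0.95 and Sp_CP from 0.10 to 0.70, it runs from 0.286 × 0.10 = 0.03 to 0.286 × 0.85 = 0.24. It is zero only when the two specificities are equal.

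**Predictive values.** Assume sensitivity 0.80, Sp_H = 0.90 and Sp_CP = 0.30. There are 20 true positives, 5 false negatives, 2.5 + 0.7m false positives and 22.5 + 0.3m true negatives.

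| m | PPV | NPV |
|---|---|---|
| 0 | 20/22.5 = 0.89 | 22.5/27.5 = 0.82 |
| 5 | 20/26 = 0.77 | 24/29 = 0.83 |
| 10 | 20/29.5 = 0.68 | 25.5/30.5 = 0.84 |

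Because the case fraction also changes with m, the predictive values would move somewhat even if the two specificities were equal.

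**Limit of the calculation.** All of this holds the cut-off fixed. Under the plan, the models and the Youden cut-off would be re-estimated with pancreatitis included, so sensitivity could shift as well.

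**The case against.** The strongest reply is that pooling follows the endpoint. Section 1.5.1 sets PDAC against no PDAC, Section 2.1.3 describes the pancreatitis group as having no known PDAC, and Objective 2 names no comparator. Including non-cancer pancreatic disease among the negatives is also a defensible design choice, since healthy-only controls can flatter specificity. This stands to the extent that a reader who infers a conflict with the endpoint's comparator goes too far. The conflict is with Objective 1 and the sample size. The SAP thus holds two comparisons, does not say which is primary, and models only one.

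Second, Section 3.4 already reports by cohort the proportions below the breath-test cut-offs. For a single breath-test cut-off, that is the false-positive proportion in each control group. This also stands and narrows the point. Section 3.4 does not cover the specificity of the multivariable models or of the faecal elastase cut-offs, and it does not change the pooled data from which the Youden cut-off is derived.

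Third, the size of the effect is assumed, and it could be small. That is correct: the documents support the direction and a range, not a value.

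On stage, a reader might infer that PDAC of any stage is counted as a case, or use the share of advanced diagnoses in Section 1.3 to guess how few early cases there would be. The SAP supports neither. Section 1.3 describes pancreatic cancer diagnoses in general, not recruitment. Sections 1.5.1 and 2.4.3 point to early or resectable disease, and stage eligibility may well sit in the protocol, which was not available. If enrolment is so limited, coding by cohort agrees with the endpoint.

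**Conclusion.** The point holds for the negative group. Objective 1 and the sample size concern PDAC versus healthy subjects, every planned primary model and the Youden search use PDAC versus everyone else, and the SAP provides no analysis that closes the gap. That mismatch rests on the SAP's text alone.

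Specificity, predictive values and data-derived cut-offs then depend on a pancreatitis share of 0% to 28.6% of negatives. How much specificity moves rests on assumed values: a drop from 80% to 66% in the main illustration, and 3 to 24 percentage points over the wider range. The 100% power statement is unaffected.

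The stage wording is a minor inconsistency between Section 1.5.1 and Sections 2.1.1 and 3.3.1. It is not evidence that later-stage cases are enrolled.

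**What to change.** In Sections 3.3.1 and 2.4.1, state that for Objective 1 the primary models are fitted, and the cut-offs derived, on PDAC versus the matched healthy controls. Then apply those models and cut-offs unchanged to the chronic pancreatitis group and report its false-positive proportion separately, with an exact confidence interval. Include the multivariable models and the faecal elastase cut-offs, which Section 3.4 does not cover. If a PDAC versus all non-PDAC model is also wanted, label it secondary and report its specificity for each control cohort.

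Reconcile the case definitions in Sections 2.1.1 and 3.3.1 with the stage I or II endpoint in Section 1.5.1.

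The cost is SAP wording and up to 10 fewer negatives in the primary model; no new data are needed. The pancreatitis estimate will be imprecise: 7 false positives out of 10, for example, has an exact 95% interval of about 35% to 93%. That uncertainty exists in any case, and separate reporting makes it visible.

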## 1.3 Study background and rationale (short synopsis)

The incidence of all types of pancreatic cancer in the UK is 9.6 per 100,000. Pancreatic adenocarcinoma (PDAC) is the most common subtype making up 85% of cases. It is regarded as the most lethal of all the common cancers on account of its insidious nature, often only presenting when causing compression of the distal biliary tree resulting in jaundice; by which point it has usually extended beyond a resectable margin and/or metastasised. This is the case in 79% of pancreatic cancer diagnoses, resulting in a 5-year survival rate of less than 5%; something which hasn't improved in 40 years. Recent studies have shown that around 40% of patients diagnosed with PC require three or more visits to their general practitioner (GP) before they are referred to a specialist thereby leading to a delay in the diagnosis of PC. A recent survey of GPs, showed that not having access to a reliable diagnostic referral pathway is a major barrier to the early diagnosis of PC.

We propose using alternative tests to determine if they are suitable for detecting PDAC in certain populations. This involves the use of a  $^{13}\text{C}$ -mixed-triglyceride breath test to test for pancreatic enzyme function and to identify potential lesions which may affect the inner workings of the pancreas. Lipase is an enzyme secreted by the pancreas used in the digestion of fats, and may provide a suitable target for investigating pancreatic function as failure to adequately digest fat could suggest possible duct obstruction or reduced secretory capability due to the presence of a tumour. In addition to this test, faecal elastase can detect patients with insufficient pancreatic function through a single stool sample, as a lower value is associated with poor pancreatic function.

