## **1.7 Description of study design**

DEPEND is a case-control prognostic study. Participants with known PDAC will be recruited alongside healthy controls, and a subset of participants with chronic pancreatitis.

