#### **2.1.2 Healthy control population**

The healthy control population will consist of 25 participants with no known diagnosis of PDAC. This population will be age- and sex- matched to those in the PDAC population.

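### PPV and NPV are listed for a case-control sample whose PDAC share (42-50%) is set by recruitment, with no target prevalence; taken from the sample, PPV would be overstated and NPV understated

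*SAP*

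**What the plan says.** SAP section 1.7 describes the design: "DEPEND is a case-control prognostic study". It adds: "Participants with known PDAC will be recruited alongside healthy controls, and a subset of participants with chronic pancreatitis". Sections 2.1.1 to 2.1.3 fix the numbers:

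- Cases: "The PDAC population will consist of 25 participants with a known diagnosis of PDAC".
- Healthy controls: "The healthy control population will consist of 25 participants with no known diagnosis of PDAC". Section 2.1.2 also has them matched to the cases on age and sex.
- Chronic pancreatitis: "The chronic pancreatitis population will consist of up to 10 participants with a known diagnosis of chronic pancreatitis".

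Under section 3.3.1, PDAC status follows from the cohort a participant was recruited to, and everyone outside the PDAC cohort is treated as negative. The same section says: "Performance measures include sensitivity, specificity, positive predictive value, and negative predictive value". It also provides for several cut-offs of the risk score to be considered with the study team in order to obtain these measures, and for calibration plots by tenth of predicted risk. The only correction it names is a bootstrap adjustment for optimism. Section 3.5 rules out further analyses.

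**The concern.** Sensitivity and specificity condition on disease status, so a sample recruited by disease status can estimate them. PPV and NPV condition on the test result and need the prevalence of disease among those tested. Here that prevalence is a recruitment ratio, and the SAP supplies no other. Bootstrapping for optimism deals with overfitting and leaves the ratio as it is.

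The background in section 1.3 concerns late diagnosis and the lack of a reliable referral route for GPs. PPV is the figure a reader would naturally carry into that setting. Because cut-offs are to be weighed using these measures, artificial PPV and NPV could also influence which cut-off is preferred. The same ratio sets the intercept of the logistic models, so the predicted risks and the calibration plots inherit it.

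**Working it through.** **The plan's own figures.** The SAP states no sensitivity, specificity, PPV, NPV or target prevalence, so there is no such figure to reproduce. Its one performance-related number is the 100% power in section 1.8 (25 per group, difference 17.8%, SD 10.5%, two-sided 5%). Taking the SD as common to both groups, the noncentrality is 17.8 / (10.5 × √(2/25)) = 5.99, and the noncentral t with 48 df gives 0.99995. That rounds to 100%. The figure reproduces and has no bearing on this point.

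**PDAC share of the sample** (sections 2.1.1 to 2.1.3):

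- No chronic pancreatitis participants: 25 / (25 + 25) = 50.0%.
- All ten enrolled: 25 / (25 + 25 + 10) = 41.7%.

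**Formulas**, with Se, Sp and prevalence p:

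- PPV = Se·p / [Se·p + (1 − Sp)(1 − p)]
- NPV = Sp(1 − p) / [Sp(1 − p) + (1 − Se)p]

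For any test with Se + Sp > 1, PPV rises and NPV falls as p rises. So whenever the target prevalence is below the sample share, sample PPV is too high and sample NPV too low. That direction does not depend on the accuracy assumed.

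**Size, with Se = Sp = 80% assumed for illustration:**

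- 25:25. True positives 20, false positives 5, so PPV = 20/25 = 80%. True negatives 20, false negatives 5, so NPV = 20/25 = 80%.
- 25:35, same specificity. False positives 7, so PPV = 20/27 = 74%. True negatives 28, so NPV = 28/33 = 85%.
- p = 5%. PPV = 0.040 / (0.040 + 0.190) = 17%. NPV = 0.760 / (0.760 + 0.010) = 98.7%.
- p = 1%. PPV = 0.008 / (0.008 + 0.198) = 3.9%. NPV = 0.792 / (0.792 + 0.002) = 99.7%.

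**Sensitivity to the assumed accuracy:**

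| Se = Sp | Measure | Sample 50% | Sample 41.7% | p = 10% | p = 5% | p = 1% |
|---|---|---|---|---|---|---|
| 70% | PPV | 70% | 63% | 21% | 11% | 2.3% |
| 70% | NPV | 70% | 77% | 95.5% | 97.8% | 99.6% |
| 80% | PPV | 80% | 74% | 31% | 17% | 3.9% |
| 80% | NPV | 80% | 85% | 97.3% | 98.7% | 99.7% |
| 90% | PPV | 90% | 87% | 50% | 32% | 8.3% |
| 90% | NPV | 90% | 93% | 98.8% | 99.4% | 99.9% |

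The prevalences of 1%, 5% and 10% are assumptions; the SAP gives none.

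**Predicted risk.** The model intercept contains the log of the sampling odds. With 25:25 the sample odds are 1; at an assumed 1% prevalence they are 1/99. Re-basing the intercept alone would move a predicted risk of 50% to odds of 1/99, that is 1%. Agreement on a calibration plot drawn in this sample is therefore agreement with the recruitment ratio.

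**The case against.** The strongest reply has four parts.

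1. *The SAP only lists PPV and NPV.* It does not say that they will be raw sample proportions or be presented as clinical values. This is correct, so the charge is that no prevalence is fixed. Raw computation is nevertheless the natural default, and nothing in the SAP leads elsewhere.

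2. *The objectives are modest.* Section 1.4 asks whether the tests separate PDAC patients from healthy volunteers and whether shorter breath tests match the 4-hour one. Neither objective claims a PPV in general practice, and referral appears only as background. This also stands, and it limits the harm. It equally means that PPV and NPV are not needed to answer the objectives.

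3. *The 80% is not a planned value.* It is close to what section 1.8 would imply for the breath test alone at a midpoint cut-off, Φ(17.8 / 10.5 / 2) = Φ(0.848) = 0.802. That requires normal data and equal SDs, and the SAP gives the SD for patients only. The models will also use faecal elastase, with cut-offs still to be chosen. The 74% further assumes the same specificity in chronic pancreatitis as in healthy controls. The figures are illustrations and no more.

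4. *Bayes projection is not a full cure.* It carries over a specificity measured in healthy, matched volunteers and at most ten people with chronic pancreatitis, which may not hold in patients seen by GPs. This stands and belongs in the label on any projection.

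Two stronger readings are tempting. A reader might infer that the design flatters predictive value in general. It does not: for given sensitivity and specificity the recruitment ratio raises PPV and lowers NPV. A reader might also take from section 1.3, "The incidence of all types of pancreatic cancer in the UK is 9.6 per 100,000", that the real PPV is a small fraction of 1%. That figure is an incidence, covers all types of pancreatic cancer and refers to the whole population. The SAP does not offer it as the prevalence among people who would be tested.

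**Conclusion.** The point holds in this form. Two of the four named performance measures for the primary endpoint depend on a prevalence that the SAP does not set and that the sample cannot supply. Computed from the sample, they would reflect a PDAC share of 42-50% and would change with chronic pancreatitis enrolment even if test accuracy did not.

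The direction is firm for any target prevalence below the sample share: PPV overstated, NPV understated. The size rests on assumed accuracy and assumed prevalence. Across the accuracies tabulated, PPV at 5% prevalence is roughly a third or less of even the lower sample value.

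Sensitivity, specificity, the model coefficients other than the intercept and the descriptive secondary endpoints do not need the recruitment ratio to match a clinical prevalence. Whether comparing known cases with healthy volunteers flatters sensitivity and specificity is a separate question and is not part of this point. The defect should be fixed before analysis, but it does not undermine the study.

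**What to change.** In SAP section 3.3.1:

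- Replace sample-based PPV and NPV with sensitivity, specificity and positive and negative likelihood ratios, each with a 95% confidence interval.
- Give PPV and NPV only as Bayes projections over a stated range of assumed prevalences, chosen and justified by the study team. Label them as projections that rely on specificity measured in healthy and chronic pancreatitis controls.
- State that the model intercept and predicted risks, including those in the calibration plots, reflect the sampling ratio and are not absolute risks.

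The cost is a wording change and one extra table, with no new data. The reported PPV will look less favourable.

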# 1 Introduction

## 1.1 Purpose of SAP

This statistical analysis plan (SAP) describes in detail the methods that will be used to analyse the data collected as part of the DEPEND study. This will form the basis of the final publication. The final analysis will follow the SAP to ensure that the analyses are conducted in a scientifically valid manner and to avoid post hoc decisions which may affect the interpretation of the statistical analysis. Any deviations from the SAP will be detailed in the final report.

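### Cut-offs and risk thresholds are selected on the same 25 PDAC cases that measure accuracy, with no threshold rule and no commitment to repeat the selection in the bootstrap

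*SAP*

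**What the plan says.** - **Cut-offs for the breath test (SAP 2.4.1).** Published cPDR cut-offs are given at 1, 2, 3 and 4 hours. The SAP will also consider cut-offs from the means of its own healthy controls, including at the intermediate half-hour points, and will look for the cut-off that "best discriminates between PDAC and other participants at each time point in this study using the Youden index".
- **Faecal elastase (SAP 2.4.2).** FE-1 may enter as <200, <100 or as a continuous value.
- **Model building (SAP 2.5.1).** Multivariable models are built "with the aim of finding the best-fitting combination of cut-offs".
- **Primary endpoint (SAP 3.3.1).** Several models are constructed, all final models are reported, and the models are validated and optimism-adjusted by bootstrapping. Sensitivity, specificity, PPV and NPV come from thresholds on the risk score: "numerous cut-offs for defining predicted cancer positivity in the underlying risk score will be evaluated with the study team".
- **Who supplies the data (SAP 2.1 and 3.3.1).** "The PDAC population will consist of 25 participants with a known diagnosis of PDAC"; "The healthy control population will consist of 25 participants with no known diagnosis of PDAC"; "The chronic pancreatitis population will consist of up to 10 participants with a known diagnosis of chronic pancreatitis". For the analysis, "all participants in the PDAC cohort are positive, all others are negative".
- **Purpose (SAP 1.1).** The plan exists "to avoid post hoc decisions which may affect the interpretation of the statistical analysis".

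No primary model or risk threshold is named, and no rule for choosing a threshold is given. The SAP does not say which steps the bootstrap repeats, or that sensitivity and specificity at a chosen threshold are among the corrected quantities.

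**The concern.** A cut-off chosen because it separates two groups well in one sample will look better in that sample than in new patients. With 25 cases the effect is not small. Bootstrap optimism correction removes such bias only to the extent that each resample repeats the selection that produced the reported rule. Two things stand in the way here. The risk-score thresholds are to be examined with the study team under no stated rule, so there is nothing to code. The steps that could be coded (Youden cut-off, best-fitting combination) are not committed to replay.

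At stake is the primary endpoint. Sensitivity and specificity could be published beside a statement of optimism adjustment that does not reach the selection behind them. The open threshold choice also sits badly with the purpose set out in section 1.1.

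**Working it through.** **1. The plan's own figure.** SAP 1.8 gives 25 per group, difference 17.8, SD 10.5, two-sided 5%, power 100%.
- Standardised difference: d = 17.8/10.5 = 1.70.
- Power = Φ(d·√(25/2) − 1.96) = Φ(5.99 − 1.96) = Φ(4.03) = 99.997%; the noncentral t gives 99.995%. The stated 100% reproduces.
- This concerns a difference in means. It says nothing about how precise or how optimistic sensitivity and specificity will be. For scale, an observed 20/25 has an exact 95% CI of 59% to 93%.

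**2. Planning effect as discrimination.** With equal-variance normal markers, AUC = Φ(d/√2) = Φ(1.70/1.414) = 0.885. AUC 0.80 is added as a less favourable case.

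**3. Selection on the data.** Assumptions not in the SAP: 25 v 25, equal-variance normal markers, equal AUC at every time point, within-person correlation 0.85, cut-off chosen by maximum J. Optimism is apparent J minus the true J of the chosen rule.

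| Selection | AUC | Apparent J | True J | Optimism |
|---|---|---|---|---|
| One time point, Youden cut-off | 0.80 | 0.54 | 0.42 | 0.12 |
| One time point, Youden cut-off | 0.885 | 0.68 | 0.58 | 0.10 |
| Best of eight time points | 0.80 | 0.62 | 0.43 | 0.19 |
| Best of eight time points | 0.885 | 0.76 | 0.58 | 0.18 |

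Across repeated runs the ranges are about 0.09-0.12 for one time point and 0.16-0.19 for the best of eight. Weaker markers fare worse: for the best of eight at AUC 0.70 it is 0.48 − 0.27 = 0.21, and for a useless marker (AUC 0.50) it is 0.23 − 0.00 = 0.23.

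**4. What the bootstrap removes (best of eight).**

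| AUC | Apparent J | Corrected, rule held fixed | Corrected, selection replayed | True J | Share removed by replay |
|---|---|---|---|---|---|
| 0.80 | 0.62 | 0.62 | 0.51 | 0.43 | 0.11/0.19 = 58% |
| 0.885 | 0.76 | 0.76 | 0.65 | 0.58 | 0.11/0.18 = 61% |

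Over all runs, one time point included, full replay removes about 60-75%. Holding the chosen rule fixed removes nothing, because a fixed rule has the same expected J in the resample as in the original sample.

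**5. A different setup.** Eight time points were combined with FE-1 (unused, <100 or <200), using adjacent-time correlation 0.9, an effect rising over 4 hours to 1.70 SD, and other assumed FE-1 and chronic pancreatitis effects. Optimism in J is 0.18 both without and with 10 chronic pancreatitis participants among the negatives. The bootstrap estimates it as 0.00 with the rule fixed, about 0.05 if only the cut-off is re-chosen, and about 0.12 if the whole selection is replayed. Without chronic pancreatitis, apparent sensitivity/specificity is 0.845/0.861 against a true 0.748/0.782.

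**The case against.** The SAP can be read more kindly, and several of these points stand.

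- **Replay is possible for some steps.** A reader might infer that the bootstrap cannot reproduce any of the selection. That goes too far: Youden cut-offs and a best-fitting combination are algorithmic and can be coded. Section 3.3.1 commits to bootstrap adjustment and nowhere says chosen cut-offs are held fixed. Only the team's judgement is beyond replay; on the rest the SAP is silent. The zero-correction result is therefore a worst case.
- **No winner need be chosen.** A reader might infer that the team will settle on a threshold once it has seen the accuracy figures. The text says only that thresholds are evaluated with the team, which also fits a table of accuracy at several thresholds. That the evaluation follows model fitting is a fair inference, since a risk score exists only after a model is fitted.
- **Best of eight is not stated.** Section 2.4.1 seeks a cut-off at each time point, and section 1.4 makes the 4-hour test the comparator for the shorter ones. Only the search for a best-fitting combination in 2.5.1 could imply choosing among times. The one-time-point figures are the safer reading.
- **Some safeguards exist.** Section 2.4.2 already includes continuous FE-1 and considers both published FE-1 cut-offs. Section 3.4 summarises proportions below the section 2.4.1 cut-offs by cohort. All final models are reported, and section 1.1 promises disclosure of deviations.

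These safeguards help transparency. They do not say how a model becomes final or how a threshold is reached, and they do not bring either step inside the optimism correction.

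**Conclusion.** The concern holds in a limited form and should be fixed. Data-driven cut-offs, the cut-off combination and the risk thresholds come from the same 25 cases and up to 35 non-cases that supply the accuracy figures. One of these choices has no rule, and replay of the others is not promised. Accuracy at selected cut-offs can thus remain too high although the models are described as optimism-adjusted.

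In J, the size is about 0.09-0.12 with one time point and about 0.16-0.19 if the best of eight is chosen, for AUC 0.885 (the planning effect) to 0.80. This rests on the assumed normality, correlation and 25 v 25 split; the direction does not. Published cut-offs used alone as fixed tests carry no cut-off optimism. The documents do not show that the final figures will be uncorrected, only that the plan does not prevent it.

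**What to change.** 1. **SAP 2.5.1 and 3.3.1:** before analysis, name one primary model (for example continuous 4-hour cPDR plus continuous FE-1). Replace the team evaluation of thresholds by an algorithmic rule, such as maximum Youden index on the risk score. Penalised fitting is optional.
2. **SAP 3.3.1:** state that every data-driven selection (time point if selected, cut-off, combination, risk threshold) is repeated in each bootstrap resample. Report optimism-corrected sensitivity and specificity with confidence intervals, and say that some optimism may remain, since replay does not remove all of it.
3. **SAP 2.4 and 3.4:** present sensitivity and specificity at the published cPDR and FE-1 cut-offs as the fixed-threshold accuracy results. Most of what is needed is already planned there.
4. **SAP 3.3.1 and 3.5:** label team-chosen thresholds and all other combinations exploratory. Section 3.5 now says no additional analyses will be reported, so its wording needs to allow for this.

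The cost is SAP wording and somewhat more bootstrap code; no further participants, samples or visits are needed. Reported accuracy will probably be lower, and the team gives up some freedom in choosing thresholds for the main result.
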